# Group-delivered cognitive behavioural therapy versus waiting list in the treatment of insomnia in primary care: study protocol for a pragmatic, multicentre randomized controlled trial

**DOI:** 10.1186/s12875-023-02018-4

**Published:** 2023-03-02

**Keywords:** Sleep problems, Insomnia disorder, Sleeplessness, Primary healthcare, Adults, Psychological treatment

## Abstract

**Background:**

Insomnia is common in the general population and is a risk factor for ill-health, which highlights the importance of treating insomnia effectively and cost-efficiently. Cognitive-behavioural therapy for insomnia (CBT-I) is recommended as first-line treatment due to its long-term effectiveness and few side-effects, but its availability is limited. The aim of this pragmatic, multicentre randomized controlled trial is to investigate the effectiveness of group-delivered CBT-I in primary care compared to a waiting-list control group.

**Methods:**

A pragmatic multicentre randomized controlled trial will be conducted with about 300 participants recruited across 26 Healthy Life Centres in Norway. Participants will complete online screening and provide consent before enrolment. Those who meet the eligibility criteria will be randomized to a group-delivered CBT-I or to a waiting list according to a 2:1 ratio. The intervention consists of four two-hour sessions. Assessments will be performed at baseline, 4 weeks, 3- and 6 months post-intervention, respectively. The primary outcome is self-reported insomnia severity at 3 months post-intervention. Secondary outcomes include health-related quality of life, fatigue, mental distress, dysfunctional beliefs and attitudes about sleep, sleep reactivity, 7-day sleep diaries, and data obtained from national health registries (sick leave, use of relevant prescribed medications, healthcare utilization). Exploratory analyses will identify factors influencing treatment effectiveness, and we will conduct a mixed-method process evaluation to identify facilitators and barriers of participants’ treatment adherence. The study protocol was approved by the Regional Committee for Medical and Health Research ethics in Mid-Norway (ID 465241).

**Discussion:**

This large-scale pragmatic trial will investigate the effectiveness of group-delivered cognitive behavioural therapy versus waiting list in the treatment of insomnia, generating findings that are generalizable to day-to-day treatment of insomnia in interdisciplinary primary care services. The trial will identify those who would benefit from the group-delivered therapy, and will investigate the rates of sick leave, medication use, and healthcare utilization among adults who undergo the group-delivered therapy.

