## Background

Insomnia is the most common sleep disorder in the general population and in clinical practice [1], with ~ 10% of adults reporting chronic insomnia in agreement with the current diagnostic classification system [2] and seems to be on the rise [3]. Among patients seeking primary care, as many as 50–70% report disturbed sleep [4, 5]. Cognitive behavioural therapy for insomnia (CBT-I) is considered most effective for long-term alleviation of chronic insomnia [6–8], but administration of CBT-I is limited by a lack of trained therapists and long waiting lists [9] (i.e., up to 1 year in Norway). To increase the availability of CBT-I, a group-delivered treatment was developed by the Norwegian Health Directorate. The treatment is based on core CBT-I principles including sleep hygiene, stimulus control, sleep restriction, cognitive restructuring, and relaxation training. Group-delivered CBT-I may complement individual CBT-I and relieve pressure on primary care, as group size may include up to 15 individuals at the same time. Although group-delivered CBT-I has already been implemented in several municipalities in Norway, its effectiveness has never been evaluated. Therefore, the objective of this study is to investigate the effectiveness of group-delivered CBT-I in Norwegian primary care.

It is of interest to identify factors that may influence the therapeutic response of group-delivered CBT-I. Up to 40% of insomnia patients do not adequately respond to CBT-I [10], likely due to insomnia heterogeneity [10–12]. For instance, insomnia patients with evening chronotype, unhelpful beliefs about sleep, short sleep, comorbidity, or high reactivity to stress may have a blunted response to CBT-I [12–15], possibly due to the influence of overactive neurobiological and psychological systems in insomnia pathophysiology [16]. Adherence to the therapeutic regime may also predict outcome [17]. Thus, a secondary objective of this study is to conduct exploratory analyses to identify factors influencing the effectiveness of group-delivered CBT-I.

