### Aims

The primary aim is to conduct a pragmatic, multicentre randomized controlled trial (RCT) to investigate the effectiveness of group-delivered CBT-I in primary care on insomnia severity at 3 months post-treatment. Secondary aims include:i.Investigate the effectiveness of group-delivered CBT-I on health-related quality of life, fatigue, mental distress, and sleep diary data at 3- and 6-months post-treatment.ii.Investigate whether potential treatment moderators (e.g., chronotype, reactivity to stress, duration of insomnia, length of prior insomnia treatment, treatment group size, physical activity) influence the effectiveness of group-delivered CBT-I.iii.Compare sick leave days, use of relevant prescribed medication (e.g., psychotropics, sedatives) and healthcare resource utilization, utilizing national registry data at pre-treatment vs. 1- and 2-years post-treatment.iv.Conduct exploratory mediation analyses to identify mechanisms behind change in the primary and secondary outcomes, focusing on psychological measures of beliefs about sleep, reactivity to stress, and sleep-related self-efficacy as potential mediators.v.Conduct a mixed-method process evaluation to assess facilitators and barriers of participants’ treatment adherence.

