### Assessments

Assessments will be carried out at 6 different time points during the RCT: T1, prior to the intervention; T2, immediately post-intervention; T3, 3 months post-intervention (primary outcome measurement); T4, 6 months post-intervention; T5, 1-year post-intervention; and T6, 2 years post-intervention. The primary outcome is self-reported insomnia severity assessed by the ISI. Several other outcomes will be used in analyses of secondary outcomes, moderators and exploratory mediators, resource use and work productivity, and in a mixed-method process evaluation, described below. Descriptions of all measures, objectives of their use, collected, the participant group receiving them, and the objectives of their use, are provided in Table 2.

**Table 2 Tab2:** Overview of the assessments utilized in the randomized controlled trial

Objective	Measure	Measurement timepoint	Participant group
Demographic information	Self-rated custom questions	T1	All
Primary outcome	Insomnia severity (Insomnia severity index)	Screening, T1, T2, T3, T4	
Secondary outcomes	Health-related quality of life (EuroQol EQ5D-5L)	T1, T2, T3, T4	
	Fatigue (Chalder Fatigue Scale)	T1, T2, T3, T4	
	Mental distress (Hopkins Symptoms Checklist)	T1, T2, T3, T4	
Moderator	Chronotype (Brief Horne-Östberg Morningness-Eveningness Questionnaire)	T1, T2, T3, T4	
Mediators	Unhelpful beliefs about sleep (Dysfunctional Beliefs and Attitudes about Sleep questionnaire-16)	T1, T2, T3, T4	
	Sleep reactivity (Ford Insomnia Response to Stress Test)	T1, T2, T3, T4	
Subjective assessment of sleep patterns	7-day sleep diary	T1, T2, T3, T4	
Mixed-method process evaluation of facilitators and barriers of participants’ treatment adherence in group-delivered CBT-I	Motivation for treatment (Nijmegen Motivation List 2)	T1	~ 60 intervention group participants
	Treatment credibility (Credibility / Expectancy Questionnaire)	T1	
	Adherence to CBT-I components (Treatment Components Adherence Scale)	T3	
	Evaluation of treatment (CBT-I evaluation scale)	T3	
	Individual semi-structured interviews	T2, T3	10–12 intervention group participants
Evaluation of sick leave rates, medication use, and healthcare services utilization	Norwegian Patient Registry	T5, T6	All intervention group participants
	Norwegian Prescription Database	T5, T6	
	National Insurance Administration	T5, T6	

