#### Sample size

The average observed change in ISI in published RCTs on the effectiveness of group-delivered CBT-I [37–41] from baseline to post-test was 6.2 points in the intervention group, compared to a 1.4-point change in the control group. This indicates a large Cohen’s *d* effect size of 0.86. However, we chose the medium Cohen’s *d* effect size of 0.50 for the sample size calculation, mostly due to the differences in the number of given CBT-I sessions across studies. Treatment in this RCT includes 4 sessions, while other reviewed studies include 5 [37, 38, 41] and 8 [39, 40] sessions, respectively. It is reasonable to assume that treatment effectiveness may decrease with fewer number of sessions. Further, since this is a pragmatic trial, we will not prevent the control group participants from seeking other forms of treatment during the RCT, nor it is a requirement that the participants do not use sleep medications. Thus, treatment effectiveness in this trial may be assumed to be lower than in the aforementioned RCTs.

A power analysis was carried out using a two-tailed t-test with 5% alpha level and 90% power to detect a medium Cohen’s *d* effect size of 0.50, with an allocation ratio of 2:1 (G*Power, version 3.1.9.6) [42]. The needed sample size was 192 in total. Additionally, to have sufficient power for moderation analyses of chronotype, we carried out a two-tailed t-test with 5% alpha level and 80% power to detect a small to medium Cohen’s *d* effect size of 0.40, with an allocation ratio of 2:1, and accounting for a 30% attrition rate based on dropout rates reported by previous studies [43–46]. The final needed sample size was 292 participants (98 in the control group, 194 in intervention group). Since missing data are unlikely to be an issue when using national registers, we did not undertake any statistical power calculations related to these analyses.

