#### Statistical analysis plan

A detailed statistical analysis plan will be published before unblinding of study data. Descriptive statistics will be presented stratified by group allocation. Categorical and binary variables will be summarized as counts and percentages, while continuous variables as means and standard deviations or medians and interquartile range, as appropriate.

The primary outcome will be analyzed using the intention-to-treat principle. Linear mixed models will be used to estimate the mean differences between T1 and T3 in ISI with 95% confidence intervals between the two groups. For continuous secondary outcomes, linear mixed models will be utilized, while binary secondary outcomes (e.g., clinically relevant change in ISI) will be analyzed using logistic mixed models. Models will include time, group, time–group interaction and baseline covariates. Since we expect that some intervention group participants will miss some treatment sessions, per-protocol analyses will be used for individuals who complete ≥ 3 sessions. Missingness patterns will be investigated, and pattern-mixture models will be used to simulate situations where the data are not missing at random. Interim analyses will not be carried out, due to limited expected adverse effects of the treatment, and because all intervention group participants are followed up by the Healthy Life Centre employees during the treatment.

Moderation analyses will be conducted to investigate whether demographics (e.g., age, sex) chronotype, treatment group size, physical activity, length of prior insomnia treatment, and duration of insomnia moderate the effectiveness of group-delivered CBT-I on primary and secondary outcomes. Exploratory mediation analyses will be conducted to investigate mechanisms of change in the primary and secondary outcomes, focusing on psychological measures of beliefs about sleep, reactivity to stress, and sleep-related self-efficacy.

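### The abstract promises to identify who benefits, but the protocol is inconsistent on whether moderation is exploratory, and its moderation analyses cannot support that promise

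*Protocol article*

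**What the plan says.** The abstract closes with an unqualified promise: "The trial will identify those who would benefit from the group-delivered therapy".

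On the status of that work the protocol speaks in two ways.

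- **Labelled exploratory.** The abstract's Methods paragraph calls the search for factors that influence effectiveness exploratory. The Background does the same: "a secondary objective of this study is to conduct exploratory analyses to identify factors influencing the effectiveness of group-delivered CBT-I".
- **Not labelled exploratory.** Aim ii is an ordinary secondary aim: "Investigate whether potential treatment moderators (e.g., chronotype, reactivity to stress, duration of insomnia, length of prior insomnia treatment, treatment group size, physical activity" and so on, while aim iv (mediation) is called exploratory. The Randomization section sets planned moderation beside exploratory mediation. The Assessments section does likewise: "Several other outcomes will be used in analyses of secondary outcomes, moderators and exploratory mediators". The Statistical analysis plan section has plain moderation analyses followed by exploratory mediation analyses.

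The Statistical analysis plan section sets the scope: "Moderation analyses will be conducted to investigate whether demographics (e.g., age, sex) chronotype, treatment group size, physical activity, length of prior insomnia treatment", and whether these and "duration of insomnia moderate the effectiveness of group-delivered CBT-I on primary and secondary outcomes". The demographic list is left open.

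The Sample size section bases the final total of 292 on a calculation made "to have sufficient power for moderation analyses of chronotype", using a two-tailed t-test at 5% alpha, 80% power, d = 0.40, 2:1 allocation and 30% attrition.

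**The concern.** A search over many moderators and several outcomes can suggest who might respond differently. It cannot establish it unless a small number of tests is singled out in advance and sized for. The protocol names no moderator-outcome pair as confirmatory, yet the abstract announces the result as an identification. Because the label is applied unevenly, a later reader could treat a nominally significant interaction either as a lead or as a planned finding, and cite the protocol for both.

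What is at stake is the conclusion the trial may draw about effect modification. The primary comparison of ISI at 3 months is not affected.

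**Working it through.** **1. Reproduce the plan's own figure.** Two-sample t-test, two-sided 5%, d = 0.40, 80% power, 2:1: 75 + 149 = 224 (power 0.803). Multiplying by 1.3: 75 × 1.3 = 97.5, rounded up to 98; 149 × 1.3 = 193.7, rounded up to 194; total 292. This matches the stated total and split. The calculation compares two group means. It contains no moderator term.

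**2. Count the pairs.** The analysis section names seven moderators: age, sex, chronotype, treatment group size, physical activity, length of prior treatment and duration of insomnia. Waiting-list participants have no treatment group, so group size cannot be tested as a treatment-by-moderator interaction. Six remain. Outcomes, at the minimum: ISI plus the three that Table 2 lists as secondary (quality of life, fatigue, mental distress), so four. At one time point, 6 × 4 = 24 pairs.

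This is a floor. Aim i adds the sleep diary and a 6-month assessment: "Investigate the effectiveness of group-delivered CBT-I on health-related quality of life, fatigue, mental distress, and sleep diary data at 3- and 6-months post-treatment". Aim ii adds reactivity to stress as a moderator, which the analysis section lists only among the mediators.

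**3. Chance of at least one false moderator.** Assume that every pair is tested at an unadjusted two-sided 5% and that no interaction exists. Neither assumption is stated in the protocol.

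- Expected false positives: 24 × 0.05 = 1.2.
- Independent tests: 1 − 0.95^24 = 0.71.
- Correlated tests, by simulation of 24 z-statistics with equal correlation among moderators and equal correlation among outcomes. The correlations are assumptions; the document gives none.

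| Moderator correlation | Outcome correlation | P(at least one) |
|---|---|---|
| 0 | 0 | 0.71 |
| 0.1 | 0.5 | 0.63 |
| 0.2 | 0.7 | 0.55 |
| 0.5 | 0.5 | 0.53–0.54 |
| 0.2 | 0.8 | 0.50 |
| 0.5 | 0.7 | 0.46 |

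At a very high outcome correlation of 0.9 it falls to about 0.43 to 0.45 (moderator correlation 0.2 and 0).

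- ISI alone, six tests: 1 − 0.95^6 = 0.265 if independent, and 0.21 at moderator correlation 0.5.

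**4. Is the chronotype test sized?** Take an assumed 50/50 binary moderator and completers 0.7 × 292 ≈ 204, that is 68 and 136. In SD units the variance of the treatment difference with all 204 is 1/68 + 1/136 = 0.0221. Each half has twice that, and the interaction is a difference between two halves, so its variance is 4 × 0.0221 = 0.0882 and its SE 0.297. Power for a 0.40 difference in effect is Φ(0.40/0.297 − 1.96) = Φ(−0.61) ≈ 0.27. The difference detectable with 80% power is 2.80 × 0.297 ≈ 0.83 SD.

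**The case against.** The strongest reply is that the analysis section gives no significance level, decision rule or adjustment policy for moderation, and it announces a detailed statistical analysis plan before unblinding. Multiplicity handling commonly belongs there, and its absence from a protocol article is no fault. This stands. A reader might infer that the plan tests all pairs at full alpha and so will more likely than not report a false responder subgroup. The document does not support that. The only 5% level given belongs to the sample-size calculations. Even under unadjusted testing the probability drops to one half or below at fairly strong correlations, and on ISI alone it is about a quarter. An interaction on quality of life or fatigue is also not an insomnia responder subgroup.

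It can also be said that the Background labels the objective exploratory, that aim ii speaks only of potential moderators, that no section uses the word confirmatory, and that the criticised sentence is a summary line in an abstract. All true, and it limits the weight of the point. It does not remove it: a later analysis plan cannot change a published promise, and four sections still separate moderation from what they call exploratory.

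Finally, no section proposes to select patients by moderator, and the service is described as open without referral, so harm through patient selection would be speculation.

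**Conclusion.** The point holds as one of wording and status, and is minor. The abstract claims that the trial will identify who benefits. The protocol elsewhere calls that search exploratory, but in the Aims, Randomization, Assessments and Statistical analysis plan sections it reserves the label for mediation. With at least 24 moderator-outcome pairs and none singled out, the design cannot carry the claim.

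The false-positive figures (0.46 to 0.71 over 24 pairs, 0.21 to 0.27 on ISI alone) show why. They are conditional on unadjusted 5% tests, no true interaction and assumed correlations, and they do not predict what the analysis plan will do.

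A reader might also infer from the Sample size section that chronotype moderation is adequately powered and could serve as the one confirmatory test. The calculation there is for a two-group difference; under the assumptions shown, power for an interaction of 0.40 is about 27%.

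**What to change.** 1. Replace the sentence in the abstract's Discussion paragraph with: *The trial will explore which baseline characteristics may be associated with a larger or smaller effect.*
2. Label moderation exploratory in aim ii, Randomization, Assessments and the Statistical analysis plan section, in line with the abstract's Methods paragraph and the Background.
3. State that moderation results are reported as interaction estimates with 95% confidence intervals, without claiming effect modification from p-values.
4. If wished, name chronotype on ISI at T3 (3 months) as the leading pre-specified moderator, and say that it is neither confirmatory nor adequately powered, because the calculation was for a two-group t-test.

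This costs a few changes of wording, with no new data, participants or procedures. The price is that the trial gives up a headline claim about who benefits.

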**Trial registration:**

The trial was retrospectively registered in the ISRCTN registry (ISRCTN16185698).

**Supplementary Information:**

The online version contains supplementary material available at 10.1186/s12875-023-02018-4.

## Background

Insomnia is the most common sleep disorder in the general population and in clinical practice [1], with ~ 10% of adults reporting chronic insomnia in agreement with the current diagnostic classification system [2] and seems to be on the rise [3]. Among patients seeking primary care, as many as 50–70% report disturbed sleep [4, 5]. Cognitive behavioural therapy for insomnia (CBT-I) is considered most effective for long-term alleviation of chronic insomnia [6–8], but administration of CBT-I is limited by a lack of trained therapists and long waiting lists [9] (i.e., up to 1 year in Norway). To increase the availability of CBT-I, a group-delivered treatment was developed by the Norwegian Health Directorate. The treatment is based on core CBT-I principles including sleep hygiene, stimulus control, sleep restriction, cognitive restructuring, and relaxation training. Group-delivered CBT-I may complement individual CBT-I and relieve pressure on primary care, as group size may include up to 15 individuals at the same time. Although group-delivered CBT-I has already been implemented in several municipalities in Norway, its effectiveness has never been evaluated. Therefore, the objective of this study is to investigate the effectiveness of group-delivered CBT-I in Norwegian primary care.

It is of interest to identify factors that may influence the therapeutic response of group-delivered CBT-I. Up to 40% of insomnia patients do not adequately respond to CBT-I [10], likely due to insomnia heterogeneity [10–12]. For instance, insomnia patients with evening chronotype, unhelpful beliefs about sleep, short sleep, comorbidity, or high reactivity to stress may have a blunted response to CBT-I [12–15], possibly due to the influence of overactive neurobiological and psychological systems in insomnia pathophysiology [16]. Adherence to the therapeutic regime may also predict outcome [17]. Thus, a secondary objective of this study is to conduct exploratory analyses to identify factors influencing the effectiveness of group-delivered CBT-I.

### Aims

The primary aim is to conduct a pragmatic, multicentre randomized controlled trial (RCT) to investigate the effectiveness of group-delivered CBT-I in primary care on insomnia severity at 3 months post-treatment. Secondary aims include:i.Investigate the effectiveness of group-delivered CBT-I on health-related quality of life, fatigue, mental distress, and sleep diary data at 3- and 6-months post-treatment.ii.Investigate whether potential treatment moderators (e.g., chronotype, reactivity to stress, duration of insomnia, length of prior insomnia treatment, treatment group size, physical activity) influence the effectiveness of group-delivered CBT-I.iii.Compare sick leave days, use of relevant prescribed medication (e.g., psychotropics, sedatives) and healthcare resource utilization, utilizing national registry data at pre-treatment vs. 1- and 2-years post-treatment.iv.Conduct exploratory mediation analyses to identify mechanisms behind change in the primary and secondary outcomes, focusing on psychological measures of beliefs about sleep, reactivity to stress, and sleep-related self-efficacy as potential mediators.v.Conduct a mixed-method process evaluation to assess facilitators and barriers of participants’ treatment adherence.

